### Enrollment

Parental consent is being obtained from families of eligible infants at both the intervention and control sites. For NICUs randomized to the FICare intervention arm, the site program coordinator approaches parents of all potentially eligible infants soon after admission to the NICU to explain the study verbally and deliver an information leaflet detailing the purpose and process of the study, as well as any possible detrimental effects of participation. Parents are screened to determine if there are barriers to their participation in the trial, and informed of the FICare education sessions, which they may attend regardless of whether they participate in the trial. Parents are then approached for informed consent when their baby becomes eligible (i.e., stable on CPAP). Families are enrolled in the trial, after consent is obtained (Day 0). All families approached are recorded in a patient eligibility log regardless of actual participation. Infants whose parents decline to participate in the study receive standard care at that site.

For NICUs randomized to the control arm, the site program coordinator approaches the parents of all potentially eligible infants for consent to collect infant data and information on parental stress and anxiety. The families of eligible infants at control sites are not screened to determine whether they would be willing to spend at least 6 h per day in the NICU as per the FICare protocol. The infants of parents who consent are enrolled in the study once they meet the inclusion criteria, and continue to receive standard care.

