### Statistical analysis

The unit of analysis will be the individual infant, and all analyses will be based on the intention to treat principle. The distribution of baseline characteristics in the study population will be summarized at the individual and cluster level within each FICare and control groups, using descriptive statistical methods. The primary outcome of weight gain at 21 days post enrollment, will be compared between the FICare and control groups using Student’s *t*-test adjusted for the inflation factor (or design effect) with a minimum variation weight correction [46, 47] to account for intra-cluster correlation and imbalance of cluster sizes. In addition, a two-level hierarchical linear regression model will examine the primary outcome, accounting for clustering, and potential confounders including patient-level characteristics (birth weight, gestational age, small for gestational age, gender, multiple births, admission illness severity, caesarean section, chorioamnionitis, maternal hypertension or diabetes, maternal education, parity) and NICU-level covariates (NICU size, teaching institution).

Secondary outcomes will be compared between the FICare and control groups using similar methods including the Student’s *t*-test for continuous variables and the Chi-square test for categorical variables adjusted for clustering [50, 51], as well as hierarchical linear or logistic regression models, as appropriate. Furthermore, weight change over time will be examined longitudinally using multivariable multi-level hierarchical models to compare the rate of change in weight gain between infants from the two trial arms.

While we realize that multiple comparisons are a concern when more than one analysis of the data is performed, we are not interested in the joint confidence region for all of our hypotheses at once. Rather, we are interested in them one at a time. Under these conditions, Rothman and Greenland [52, 53] argue that “multiple inference procedures … are irrelevant, inappropriate and wasteful of information” because they produce improperly imprecise single intervals.

Prior to data unmasking and analyses, issues relating to missing data and potential sources of bias will be examined and appropriate correction methods determined.

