To assess selection bias, differences in the enrolment rate at FICare and control sites will be examined. Multivariable analyses will correct possible confounding bias by adjusting for baseline factors including social, economic (parental education, employment), demographic (maternal age, family size), obstetric (parity, pregnancy complications) and infant factors (gestational age, small for gestational age, illness severity at admission, and age at enrollment). Further analyses will consider propensity score methods accounting for imbalance of baseline characteristics between FICare and control groups [54]. While we will attempt to identify and adjust for all the possible confounding variables, we also acknowledge that any selection/participation bias could be due to some unmeasured element of “parent engagement” at the initiation of the intervention.

Subject attrition may also produce biased results and impact generalizability. Families in the FICare group are provided with as much physical, psychological and financial support as possible (including parent lounge; subsidized parking or a transit pass; access to peer-to-peer, social, and psychiatric support services), but no such supports are available to control families. Attrition bias will be minimized by performing statistical analyses according to the intention to treat principle. To minimize losses due to retro transfer from level 3 to level 2 units prior to completion of the 21-day trial period, the original study protocol has been amended to allow follow-up of these infants within level 2 units provided these units obtain Research Ethics Board approval, receive appropriate training, and comply with the study protocol including providing nurse education and parent education programs.

Possible bias due to differential withdrawal or study drop-out will be assessed by examining the distribution of baseline factors between families who consent and complete the study, and eligible families who consent and start but do not complete the study within the intervention and control sites. Furthermore, a sensitivity analysis will compare results from complete-case data and from all families who were enrolled where missing data are imputed using methods that account for clustering [56, 57].

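### The enrolment trigger is worded differently by arm, and the primary-outcome model lists neither Day 0 weight z-score nor age at enrolment

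*Protocol article*

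**What the plan says.** **Start of the window (Protocol article, Enrollment).** For intervention sites: "Parents are then approached for informed consent when their baby becomes eligible (i.e., stable on CPAP"), and then "Families are enrolled in the trial, after consent is obtained (Day 0"). For control sites, the coordinator "approaches the parents of all potentially eligible infants for consent to collect infant data and information on parental stress and anxiety", and "The infants of parents who consent are enrolled in the study once they meet the inclusion criteria, and continue to receive standard care". No timing of control consent relative to eligibility is given. The Outcomes and measures section treats enrolment as Day 0 in both arms.

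**Endpoint (Sample size calculation).** The change score is the z-score at Day 21 minus the z-score at enrolment.

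**Analysis (Statistical analysis).** The primary outcome is compared by a t-test corrected for clustering, without covariates. In addition, a two-level linear model adjusts for "patient-level characteristics (birth weight, gestational age, small for gestational age, gender, multiple births, admission illness severity" and several obstetric and maternal factors, plus two unit-level covariates. Neither age nor z-score at Day 0 is named.

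**Second covariate list (Limitations and feasibility).** The multivariable analyses meant to correct confounding adjust for social, demographic, obstetric and infant factors. The infant factors end with "illness severity at admission, and age at enrollment". Day 0 z-score is not named here either.

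**The concern.** Units were randomised first and families recruited afterwards by staff who knew the allocation. The Limitations section concedes that the two groups of families may differ. Only intervention families must commit to six hours a day. In that setting, baseline balance at Day 0 cannot be taken for granted, and a trigger worded differently by arm is one more route to imbalance.

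The endpoint is sensitive to this because the change in z-score may depend on how old the infant is when the 21 days start and on where its z-score stands at that moment. The pilot study matched controls on age at enrolment, among other factors. The trial's primary comparison has no equivalent. Birth weight, gestational age and small-for-gestational-age status describe the infant at birth, not at Day 0. An imbalance left in the comparison would be read as an effect of the intervention, or would hide one.

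**Working it through.** **1. Order of events by arm (Enrollment).**

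| | Intervention | Control |
|---|---|---|
| Consent sought | when the infant becomes eligible | from parents of potentially eligible infants; timing not stated |
| Enrolment | after consent | when a consented infant meets the criteria |

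If a control family consents before eligibility, the infant's Day 0 is the eligibility date. If it consents at or after eligibility, the two orders coincide. The text allows both.

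**2. Covariates by section.**

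| | Statistical analysis, t-test | Statistical analysis, model | Limitations and feasibility |
|---|---|---|---|
| Age at enrolment | no | not listed | listed |
| Day 0 weight z-score | by subtraction only | by subtraction only | not listed |

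**3. Why subtraction is not adjustment.** Let the expected change be α + δ·(arm) + β·(Day 0 z) + γ·(age at Day 0). The unadjusted difference between arms then estimates

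δ + β·(arm difference in Day 0 z) + γ·(arm difference in age).

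The extra terms vanish only if each slope or each arm difference is zero. Regression to the mean implies β < 0. The document gives neither slope and neither arm difference, so no bias can be calculated from it.

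**4. Scale, starting from the plan's own figure.** Inputs from the sample size section: 675 per arm, 10% drop-out, SDs 0.57 and 0.43, difference 0.11, ICC 0.01, and 6 large and 10 small sites of average size 315 and 113. Assumed: 3 large and 5 small sites per arm, two-sided 5% test, normal approximation.

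- Evaluable: 675 × 0.9 = 607.5 per arm.
- Cluster sizes: 607.5 × 315/1510 = 126.7 and 607.5 × 113/1510 = 45.5, where 1510 = 3 × 315 + 5 × 113.
- Effective n = 3 × 126.7/(1 + 125.7 × 0.01) + 5 × 45.5/(1 + 44.5 × 0.01) ≈ 326 per arm.
- SD = √[(0.57² + 0.43²)/2] = 0.505.
- SE = 0.505 × √(2/326) = 0.0396.
- Power = Φ(0.11/0.0396 − 1.96) = 79.4%, which agrees with the stated 80%. The sample size is not in question.

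For an assumed uncorrected shift b, in either direction:

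| Shift b (z) | Share of 0.11 | Type I error | Power for 0.11 if the shift is against FICare |
|---|---|---|---|
| 0 | 0% | 5.0% | 79% |
| 0.01 | 9% | 5.7% | 71% |
| 0.02 | 18% | 8.0% | 62% |
| 0.04 | 36% | 17.3% | 42% |

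Type I error is 1 − Φ(1.96 − b/SE) + Φ(−1.96 − b/SE). The last column is Φ((0.11 − b)/SE − 1.96). The values of b are illustrations, not estimates, and zero is among the possibilities.

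**5. Precision.** If Day 0 z-score correlates r with the change, adjusting for it removes r² of the infant-level residual variance: 0.3² = 9% to 0.4² = 16% for an assumed r of 0.3 to 0.4, and nothing if r = 0. The gain over a model already containing birth weight and gestational age would be smaller.

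**The case against.** The strongest reply is that no lag is shown. The Enrollment section opens by saying that consent is sought from families of eligible infants in both arms, and nothing says that control consent precedes eligibility. Intervention families are also informed and screened soon after admission, which shortens the later consent step. No such preparation is described for control sites, so a lag in the opposite direction fits the text equally well. This stands.

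A reader might infer that Day 0 falls later at intervention sites, that early weight loss is thereby moved out of the window, and that an apparent benefit follows. The document supports neither the lag, nor its direction, nor any size for it.

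Second, age at enrolment is planned for, in the Limitations section, and propensity score methods are to be considered. Both covariate lists are introduced in open-ended terms, so they are inconsistent with each other rather than flatly contradictory. This also stands: it would be wrong to say that age is ignored. It remains true that the list tied to the primary outcome omits it.

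Third, a change score is a familiar choice, size at birth partly stands in for size at Day 0, and final covariates may be fixed in an analysis plan that is not shown. This weakens the point without removing it. The plan prints two lists that disagree on age, and neither contains the baseline value of the outcome itself.

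**Conclusion.** The point holds in a limited form. The trigger is worded differently by arm, the primary t-test is an unadjusted comparison of change scores, and the primary-outcome model names neither Day 0 z-score nor age at enrolment, although the Limitations section names the latter. Comparability at Day 0 is therefore not assured.

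It would go too far to call the 21-day windows non-comparable. Both arms share the infant eligibility criteria and a 21-day window from enrolment, and the triggers may coincide in practice.

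No bias figure can be given. The type I error of about 8% at a shift of 0.02 z and 17% at 0.04 z shows only how sensitive the comparison would be. It rests on the assumed split of sites, a two-sided test and the pilot SDs. The sample size is unaffected. This is a free improvement to the analysis, not a demonstrated error in the result it would give.

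**What to change.** - Add Day 0 weight z-score and postnatal age at enrolment as covariates in the two-level model for the primary outcome. The z-score is needed for the endpoint anyway, and age at enrolment is already a planned adjustment factor.
- Use one covariate list in the Statistical analysis and Limitations sections.
- Use the same wording for enrolment and Day 0 in both arms, saying how consent and eligibility combine to set the date.
- Report age and weight z-score at Day 0 by arm.

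The cost is a few lines of text and one extra baseline table entry per variable, settled before data are unmasked. No new data are needed. Day 0 need not be moved back to the eligibility date: data collection starts at enrolment, and the move would also shift the Day 21 weight and separate it from the parent questionnaires.

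Two limits remain. The t-test stays unadjusted, so the plan should say which of the two analyses carries the conclusion. Covariates also limit, but do not remove, bias from recruitment after randomisation, since the plan itself acknowledges that parental engagement may be unmeasured.

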### Privacy and confidentiality

All data are collected on a regular basis throughout the duration of the trial according to standardized definitions. The de-identified data are transferred to the CNN Coordinating Centre at the Maternal-Infant Care Research Centre, Toronto for analysis. All data access and use complies with the Health Information Act and the Personal Information Protection and Electronic Documents Act (PIPEDA) in Canada, the Privacy Act 1988 Sections 95 and 95A in Australia, and the Privacy Act 1993 and Health Information Privacy Code in New Zealand. Data security is compliant with standards established by the CNN and the Mount Sinai Hospital Research Ethics Board. Only de-identified information will be used in the analysis and publication of results. Publications will only use aggregate data.

### Patient withdrawals

Parents can withdraw themselves from the study at any time on their own request. If at any time it is identified that a parent is having difficulty taking on their new role or is feeling very stressed, the physician taking care of the infant will meet with the parent to see what additional supports are needed. Parents also have access to peer-to-peer support from veteran parents, social work support, and psychiatric consultation on an as-needed basis. If it is felt by the care team that it is not in the parent’s best interest to continue with the FICare model of care, this will be discussed with the parent and other options explored. If there is any identified risk to the infant by the parent’s continued participation, standard care will be applied. If an infant’s medical condition deteriorates such that he/she needs ventilation, or can no longer be provided adequate medical care in this model, the family’s involvement will be modified until the infant’s condition improves and they can resume full involvement.

### Intervention

Enrolled parents are oriented to the unit by a specially trained FICare program coordinator, who guides the parents in accessing the tools necessary for their self-education, and provides information on the charting/diary entries required and how they will be asked to assume responsibility for more of their infant’s care. Parents are expected to attend daily medical rounds, do basic infant charting, and maintain a diary to the best of their ability with the aim of providing them with greater knowledge of their infant’s medical status. Nursing support enables parents to provide care for their infant(s) through activities such as feeding, bathing, dressing, and holding skin to skin. Additional support, particularly around coping within the NICU, is provided to the parents by volunteer veteran parents [35] and through special education sessions (see *‘**Parent education program**’* below).

#### Resources

Resources are provided to facilitate parents’ ability to spend as much time as possible at the intervention sites. Each unit provides a lounge and sleep room for the exclusive use of parents, as well as amenities to facilitate parents spending extended periods of time in the hospital. Comfortable reclining chairs are provided in the NICU for parents to provide kangaroo and skin-to-skin care, while still being able to interact with other parents and staff, and breast pumps are available to facilitate breast feeding. Parents are also provided with subsidized parking or public transport vouchers.

#### Provider/nurse and parent volunteer education program

All doctors, nurses, respiratory therapists, social workers, and veteran parent volunteers at NICUs in the intervention arm have been trained in FICare. A team consisting of a neonatologist and the FICare program coordinator from each Canadian NICU attended a 2-day training program in Toronto. The training of the Australian units were conducted by the Toronto group in Sydney, Australia, while material from the Toronto group was used to construct a training workshop for the New Zealand unit in Dunedin, New Zealand. Training was provided by a multi-disciplinary team (neonatologist, nurse, psychologist, social worker, veteran parent volunteer) from Mount Sinai Hospital with experience in training staff gained during the pilot study. The training program was designed to provide the skills needed to teach other staff the concepts of FICare, including improving parent-infant interaction, re-conceptualization of the nursing role, coaching skills, psychological implications of preterm birth on parents, infant development, and discussions about life as a FICare nurse and a day in the life of a NICU parent [30]. Following this workshop, each NICU team organised training for their nursing staff, equivalent to a 4-h training workshop. Veteran parent volunteers were also orientated and trained within their own hospitals. Physicians and other health professionals were trained through presentations at existing staff meetings, rounds, and journal club-style forums.

#### Parent education program

##### Parent education sessions

At the intervention sites, a parent education program is provided with small group sessions three to five times per week. These sessions provide parents with information about the medical care of preterm infants, preterm newborn development, coping within the NICU, preparation for discharge, and how they can interact with their infant more effectively [29]. The sessions follow a three-week schedule but the content and timing of the sessions are adapted to the enrolled families’ needs. The sessions are led by the FICare program coordinator or a healthcare professional with expertise in the topic being discussed (e.g., lactation consultant, dietician, pharmacist, respiratory therapist, mental-health professional). Appropriate educational materials including handouts and reference material may also be provided. Information provided in the education sessions is reinforced at the bedside by nursing staff.

##### Parent checklist

Parents are also provided with a skills checklist to guide them and help them track their education and skill development. The checklist is used to evaluate parents’ progress throughout the program and make appropriate changes to the support provided as required.

##### Charting

Parents are expected to complete a chart for their infant on a daily basis including recording the infant’s activity, feeds, and output. They are also encouraged to keep a diary, which facilitates parental recall of special events with their infant. Both the parental chart and diary are used for communication during medical rounds, but are not part of the official medical record. Parents record their time spent at the bedside, performance of skin-to-skin care, and attendance at the education sessions. The primary nurse for each infant continues to complete the official medical record as per hospital protocol.

#### Psychosocial support

Parent-to-parent support plays a large role in the FICare model of care. The physical clustering of FICare families together in the NICU and their participation in small group education sessions facilitate interaction and sharing of experiences. Volunteer veteran parents, who have had prior experience of having an infant admitted to the NICU, visit each NICU, organize recreational activities, and provide telephone support for families. This peer-to-peer support system aims to develop a sense of community among the FICare families [31]. Additional supports such as social work and psychiatric consultation are provided on an as-needed basis.

### Data collection

Data collection at both the intervention and control sites commences at enrollment and continues for the trial duration (21 days) and through to discharge from the NICU. Data collection utilizes the existing CNN database platform [36] in Canada, and in Australia and New Zealand, the Australian and New Zealand Neonatal Network (ANZNN) data system [37]. Data collected include demographics, antenatal and obstetric risks, delivery complications, admission illness severity scores, and selected practices and outcomes related to this trial. At each site, a trained research assistant abstracts data daily from patient charts directly into a laptop computer using a customized data entry program with built-in error checking and a standard manual of definitions. SSL-encrypted data are electronically transmitted directly from the Canadian sites to the CNN Coordinating Centre for verification and further cleaning. The Australia and New Zealand sites collate data via the ANZNN data verification system and submit encrypted data in batches to the CNN Coordinating Center.

Questionnaires and surveys are administered to parents by site program coordinators, and are available online and on paper. Data entered into online surveys are automatically included in a survey database and answers from paper documents are entered into the database by the program coordinator. In addition, in the Australia and New Zealand sites parents have the preferred option of entering answers directly via smartphone to a purpose-built web-based dataset that is being collated at the ANZNN Coordinating Centre.

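### At FICare sites the coordinator who supports parents also appears to administer the stress and anxiety questionnaires and key the paper answers, an avoidable arm-specific response bias in a secondary outcome

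*Protocol article*

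**What the plan says.** All references are to the protocol article.

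- **Data collection**, on who handles the questionnaires: "Questionnaires and surveys are administered to parents by site program coordinators, and are available online and on paper". On paper forms: "answers from paper documents are entered into the database by the program coordinator". On the electronic route: "Data entered into online surveys are automatically included in a survey database". For Australia and New Zealand: "parents have the preferred option of entering answers directly via smartphone to a purpose-built web-based dataset".
- **Intervention**, on the coordinator's part in FICare: "Enrolled parents are oriented to the unit by a specially trained FICare program coordinator, who guides the parents in accessing the tools" that they need to educate themselves.
- **Parent education sessions**: "The sessions are led by the FICare program coordinator or a healthcare professional with expertise in the topic being discussed".
- **Enrollment**: "For NICUs randomized to the FICare intervention arm, the site program coordinator approaches parents of all potentially eligible infants". Control sites also have a site program coordinator, whose described task there is to seek consent for collecting infant data and parental stress and anxiety information.
- **Outcomes and measures**: parent stress and anxiety is one of six groups of secondary outcomes. Both instruments are given at Day 0 and Day 21. The PSS:NICU is described as self-report, and one of its four subscales concerns how parents relate to and communicate with staff.

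**The concern.** Lack of blinding is inherent here, and the article says so under Trial design. Who collects the answers is a separate matter and is open to choice.

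By Day 21 a FICare parent has had up to three weeks of support from the coordinator. If that parent answers on paper, the same coordinator reads and types in the answers, including ratings of the relationship with staff. A control parent has no comparable relationship with the person collecting the form. Any pull towards favourable answers would therefore act in one arm only and would grow between the two measurements. Part of an apparent fall in stress under FICare could then come from how the question was put and returned rather than from how the parent felt.

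Reducing parental stress and anxiety is among the benefits that the Discussion hopes for, so the credibility of this comparison matters even though it is secondary.

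**Working it through.** No figure in the article quantifies this point, so the check sets the passages side by side.

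**1. Is it the same person?** The article uses three titles: site program coordinator (Enrollment, Data collection), program coordinator (Data collection) and FICare program coordinator (Intervention, Parent education sessions). It nowhere says that these are one person at a FICare site. It is the natural reading, because each site is described as having one such post and no second coordinator is mentioned.

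**2. Does the role differ between arms?**

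| Task | FICare site coordinator | Control site coordinator |
|---|---|---|
| Seeks consent | yes | yes |
| Administers PSS:NICU and STAI | yes | yes |
| Keys paper answers | yes | yes |
| Orients and guides parents | yes | not described |
| Leads education sessions | yes, or a topic expert does | not described |

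The last two rows exist in one arm only. Uniform data collection across arms therefore does not cancel the effect.

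**3. Which answers are exposed?**
- *Paper*: the coordinator administers the form, sees the answers and keys them. This is the greatest exposure.
- *Online*: the coordinator administers the survey, but the answers reach the database without keying. Exposure is smaller.
- *Smartphone*: direct entry, the preferred option at the Australian and New Zealand sites, which are 6 + 1 = 7 of 19 + 7 = 26 sites. Exposure is smaller again.

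For the other 19 of 26 sites (19/26 = 73%), all Canadian, the article states no preference between online and paper. The share of forms completed on paper is not given, so the exposed fraction is unknown.

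**4. Can the planned analysis remove it?** The Statistical analysis and Limitations and feasibility sections plan covariate adjustment, possible propensity score methods, intention to treat, and imputation that allows for clustering. The first two address baseline imbalance and the last two address attrition. A reporting difference that enters with the Day-21 answer is neither, so none of these removes it.

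**5. Is it acknowledged?** Limitations and feasibility discusses allocation, selection, confounding and attrition bias, but not response bias in the questionnaires. A safeguard against measurement bias is described for weighing (recalibrate, weigh three times, average). For the questionnaires, only the electronic entry options act as one.

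**The case against.** The strongest reply has four parts.

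*Administered may mean only handed out or sent.* The PSS:NICU is a self-report form offered online and on paper, and nothing says that the coordinator interviews parents or is present while they answer. This stands. A reader might infer that all self-reports at FICare sites are delivered to the person who ran the intervention. The article does not support that: online and smartphone answers bypass the coordinator's keying, and nurses, veteran parents and topic experts also deliver FICare.

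*Parents know their care model whoever collects the form.* True, and changing the collector would leave that part of the bias in place. The point concerns only the avoidable addition.

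*The size is unknown.* Also true. A reader might try to scale the bias against the pilot, where mean PSS:NICU fell by 3.06 − 2.30 = 0.76 in FICare mothers and 3.25 − 2.99 = 0.26 in controls, a difference of 0.50. That does not help: the document gives no basis for any assumed size of courtesy effect, and the pilot scores end at discharge whereas the trial measures at Day 21.

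*The article is a condensed account and makes general commitments.* It promises to examine possible sources of bias before unmasking and to report residual bias, and what parents are told about confidentiality may stand elsewhere. So no fault is found in what the article leaves out about confidentiality. What remains is a stated procedure: the coordinator administers the questionnaires and keys the paper answers.

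**Conclusion.** The point holds as a cheap improvement to data collection. At FICare sites the coordinator appears both to support parents and to administer their stress and anxiety questionnaires and key the paper answers, with no described counterpart at control sites. This opens a response bias in one arm at Day 21, beyond the unavoidable lack of blinding, and the planned analyses cannot remove it. The likely direction is lower reported stress and anxiety at FICare sites.

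The size cannot be estimated from the document. The conclusion assumes that the coordinator titles refer to one person at FICare sites and that some families use paper. It touches one of six secondary outcome groups. A reader might infer that the trial's main result is in doubt; it is not affected by this point, because the primary outcome is a weight z-score and does not depend on these questionnaires.

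**What to change.** In both arms, and starting at the same time in both:

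1. Make direct online or smartphone entry the default for PSS:NICU and STAI at Day 0 and Day 21.
2. Where paper is used, have it returned sealed and entered by the site research assistant, who already abstracts data at each site, or by the coordinating centre. The coordinator can still send reminders.
3. Record the completion mode for each questionnaire, so that a sensitivity analysis by mode is possible. Families may choose their mode and it may vary by country, so that analysis is supportive only.
4. Name response bias in the self-reports under Limitations and feasibility.

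Enrollment began in April 2013 and was expected to end in August 2015. If it is well advanced, apply items 1 and 2 to newly enrolled families only, so that each family's Day 0 and Day 21 answers use the same mode. Item 4 can be done at any stage.

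The cost is small, because the electronic routes, research assistants and coordinating centre already exist. The downsides are possibly slightly lower completion and, if the change is made mid-trial, a mix of modes within each arm. Eligibility, the intervention and the primary analysis stay as they are.
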